**FIGURE 1 F1:**
[figure not shown]
A breakdown of each experimental session for the **(A)** Oral Cannabis + Alcohol (Part 1) and **(B)** Vaporized Cannabis + Alcohol (Part 2) studies. * indicates a collection of vitals (heart rate and blood pressure), blood, and breath alcohol concentrations (BAC). Δ indicates the collection of all subjective questionnaires (drug effect questionnaire; DEQ; subjective high assessment scale; SHAS; biphasic alcohol effects scale; BAES). @ indicates the administration of the DRUID application. ^ indicates the administration of all six Standardized Field Sobriety Tests (SFSTs). All outcomes are collected during baseline procedures.

### 2.4 Drug preparation and dosing procedures

High Δ9-THC and placebo cannabis were obtained for this study from the National Institute on Drug Abuse (NIDA) Drug Supply Program. The cannabis contains: 18.16% Δ9-THC, <0.03% cannabidiol (CBD), 0.11% tetrahydrocannabivarin (THCV), 0.38% cannabinol (CBN), 0.24% cannabichromene (CBC), and 0.38% cannabigerol (CBG). This cannabinoid profile is comparable to high Δ9-THC cannabis sold in dispensaries and high Δ9-THC plant material seized by law enforcement in the United States (Vergara et al., 2017; ElSohly et al., 2021). The placebo cannabis contains: <0.01% Δ9-THC, CBD, CBN, THCV, CBC, and CBN. Participants will be given the same quantity of cannabis in each experimental condition. Using this batch of cannabis, 137.8 mg will be used to achieve a 25 mg Δ9-THC dose, 55.1 mg of active cannabis and 82.7 mg of placebo cannabis will be used to achieve a 10 mg Δ9-THC dose, and 137.8 mg of placebo cannabis will be used for placebo conditions.

In Part 1, cannabis brownie preparation will consist of: (1) grounding cannabis into a fine powder; (2) baking cannabis at 250°C so that tetrahydrocannabinolic acid (THC-A) will decarboxylate to Δ9-THC, and (3) mixing decarboxylated cannabis with a commercial brownie batter, along with other ingredients (eggs, vegetable oil, etc.). Each brownie will be baked individually to ensure accurate dosing (precisely weighed amounts of ground cannabis will be included in each brownie). In prior studies, we have ensured that these methods reliably yield targeted Δ-9-THC doses (Vandrey et al., 2017; Spindle et al., 2021). Active and placebo brownies will be made with the same quantity (g) of cannabis to assist with blinding.

In Part 2, participants will self-administer vaporized cannabis using the Mighty Medic vaporizer (Storz-Bickel, Tuttlingen, Germany), a handheld commercial vaporizer designed specifically for the delivery of cannabis and Δ9-THC. The Mighty Medic is an approved medical device in the European Union, Canada, and Israel. Precisely weighed amounts of cannabis are placed in disposable dosing capsules (or “pods”), heated at 204°C, and participants inhale the resulting vapor. In each Part 2 session, participants will inhale the entire contents of a dosing capsule in an *ad libitum* manner; use of a paced puffing procedure in a previous study resulted in more coughing and symptoms of hyperventilation compared with *ad-libitum* puffing. In prior studies (Spindle et al., 2018; Spindle et al., 2019; Arkell et al., 2020), we have shown that our *ad-libitum* dosing procedure results in consistent dose delivery across individuals and sessions and produces dose-orderly drug effects. New mouthpieces and pods will be used in each session to prevent contamination from prior doses. The BPRU pharmacy will store, prepare, and dispense cannabis for both studies.

Alcohol drinks with doses targeted to produce BACs of 0.05% or 0.08% will be self-administered by participants. Three alcohol drinks (each containing a third of the total active alcohol dose) will be made by mixing an exact amount of 95% grain alcohol (minus 1 ml for blinding, see below) with a non-caloric sweetened beverage (i.e., sugar-free Cherry Kool Aid) to achieve a volume of 4 oz each (12 oz total). Placebo drinks will be prepared by floating 1 ml of alcohol on top of the 4 oz flavored beverage immediately prior to dosing as part of blinding procedures; to further facilitate blinding, an alcohol-soaked hair tie will be placed around each glass, delivering a strong alcohol odor for placebo and active drinks. Drinks will be consumed over a 15-min period. Specifically, participants will ingest each drink within a 5-min time frame and will wait until the next 5-min window before administering the next drink. Alcohol doses for each participant will be calculated with the Computerized Blood Alcohol Calculator (CBAC©) (Addiction Research Foundation; Fisher et al., 1987). The amount of alcohol needed to produce a given BAC is calculated by factoring in sex, age, height, weight, calculated total body water, and time spent drinking. In prior alcohol dosing studies, we have confirmed that the CBAC reliably produces specific BACs (e.g., 0.05% or 0.08%) across the lifespan in men and women with a range of alcohol use and drinking patterns (Uhart et al., 2013; Weerts et al., 2017; McCaul et al., 2018).

### 2.5 Outcome measures

All study outcomes described below will be assessed at baseline and at specified timepoints after drug exposure (Figure 1). The proposed timepoints were designed to capture the full time course of drug effects for each route of cannabis administration.

### 2.6 Simulated-driving performance: Overview

The STISIM M40000-R Drive driving simulator (software: STISIM Drive version 3.14; Figure 2) will be used in this research to assess driving performance (System Technology, Inc. Hawthorne, CA). The simulator consists of three video monitors that provide a 135° field-of-view, as well as a car seat, steering wheel, turn signal lever, accelerator, and gas and brake pedals. The participant can fully control the speed and maneuvering of the vehicle. Seat and monitor positioning, monitor size, turning signals, responsiveness of gas and brake pedals and steering wheel, and viewing angles were all engineered to conform to automotive ergonomics and accurately simulate the experience of driving an actual vehicle. Prior research has independently confirmed that STISIM Drive® simulators are valid reflections of real-world driving conditions (Shechtman et al., 2009; Mayhew et al., 2011).

**FIGURE 2 F2:**
[figure not shown]
STISIM M40000-R Drive driving simulator with a sample driving scenario. **(A)** depicts the operator interface where session administrators (left) set preselected driving scenarios. **(B)** illustrates the three-screen display and arrows indicate the divided attention task’s buttons (pink tape).

The fully interactive driving simulations created for this research feature a range of routine and non-routine events, including driving through residential, rural, construction zone, and metro sections, as well as two controlled driving scenarios. During routine driving sections, participants will encounter various events and challenges a driver may encounter on the road such as signal lights (some requiring turning maneuvers) and stop signs, other vehicles that must be navigated around, pedestrians, or other similar challenges. The two controlled scenarios include a Car Following Task and a Divided Attention Task. Data are collected during the routine driving sections at specific events that may be impacted by alcohol and cannabis intoxication (e.g., response to unexpected stimuli to avoid collisions, interactions with stoplights) and data is collected throughout the two controlled scenarios. Car following and divided attention tasks have shown good sensitivity to alcohol (Freydier et al., 2014; Miller et al., 2020; Garrisson et al., 2021) and cannabis impairment (Arkell et al., 2020; Marcotte et al., 2022) in prior studies because these two controlled scenarios test key aspects of driving performance known to be affected by these drugs (e.g., divided/sustained attention, processing speed, psychomotor ability, maintaining lane position, speed, and distance to other cars; Thawer et al., 2022). Beyond these specific events and scenarios, additional summary variables of interest are passively collected throughout the drives (see below).

A total of ten unique drives were created for this project to avoid potential practice/learning effects (e.g., memorizing avoidance scenarios). Drives differ by the order with which events and scenarios are presented and by the type of accident avoidances that occur, but the drives are otherwise identical so that each version will produce comparable results. For example, the length of each drive, the environments encountered, and key drive features are the same for each simulation. Other vehicles in the simulations are randomly generated, which further increases the novelty of each drive. Beyond mitigating practice/learning effects, the different drive iterations also ensures that each drive is novel to the participant on a given session day; at each driving timepoint, participants are randomized to receive any of these 10 drives, but the same drive will not occur twice in a given session. Each drive is approximately 18 miles long and takes about 25 min to complete. All 10 versions of the driving simulation (as well as an R script to extract and organize the data) are available to download at: https://github.com/[name]/STISIM_impaired_driving. Drives will be performed at baseline and again 1.5, 3.5, 5.5, and 7.5 h after Time 0 (see Figure 1).

### 2.7 Driving simulator tasks and outcome measures

#### 2.7.1 General driving summary data

Each simulated drive collects a series of variables associated with participants’ global driving behaviors throughout the entire drive. These variables can be classed into 4 categories: Accidents (number of collisions, pedestrians hit, and off-road accidents), Rule-Following (number of missed stop signs, stops at red lights, and illegal turns), Speed (number of speed exceedances, total run length and speed, and percentage of time driven over the speed limit), and Lateral Movement (number of centerline crossings, road edge excursions, and percentage of time driven out of lane; Dahlgren et al., 2020). These variables are collected continuously and independent of the of programmed driving events.

#### 2.7.2 Baseline acclimation drive

Prior to the start of each session’s baseline procedures, participants will complete an acclimation drive to reorient themselves to the driving tasks and handling of the vehicle (e.g., steering/braking sensitivity) that will include: a 3-min stopping and turning segment, a 1-min car-following task, a 1-min divided attention task, and a 3-min normal driving segment that includes one crash avoidance scenario. No data will be collected from this drive.

#### 2.7.3 Car-following task

During each drive, participants will perform a 5-min car-following task. This task commences when a vehicle appears about 300 ft in front of the participant’s vehicle (Figure 3). Participants are instructed to follow the lead vehicle and to try to maintain a constant distance (headway) to it. The lead vehicle accelerates and decelerates every 30 s in a sinusoidal manner. The lead vehicle’s speed fluctuates between 50 and 70 mph (80 and 110 km/h). The task occurs on a two-lane road; cars periodically drive by in the opposite lane but there are no cars aside from the lead vehicle in the participant’s lane.

**FIGURE 3 F3:**
[figure not shown]
The car-following task occurs behind a white SUV over a duration of 5 min. The primary outcomes for this scenario are standard deviation of lateral position (SDLP), the car’s modulus, and the coherence to the task.

The primary outcome measures for this task include SDLP (a composite measure of lane weaving, swerving, and over-correcting), car-following modulus, response delay, and coherence. The modulus variable indicates how well the participant’s speed matches the lead vehicle’s speed; a value of 1 represents a perfect match, values greater than 1 indicate the participant generally drove faster than the lead vehicle, which indicates tailgating behavior, and values under 1 indicate the participant tended to drive slower than the lead vehicle. Car-following delay represents the amount of time it takes for the participant to respond to speed changes by the lead vehicle. Car-following coherence demonstrates how well the participant’s overall data matches that of the lead vehicle; coherence is expressed as a correlation from 0–1 (0 = no correlation between participant’s and lead vehicle’s data; 1 = perfect correlation between the two vehicles’ data).

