Driving simulators have been demonstrated to be accurate proxies for real-world driving and are an effective way to evaluate the impairing effects of various substances under safe conditions (Veldstra et al., 2015; Helland et al., 2016). Collectively, prior studies have revealed that alcohol and/or high Δ9-THC cannabis can impact various facets of driving. Alcohol has reliably been shown to adversely impact lane weaving (or standard deviation of lateral position, SDLP), performance on driving tasks of divided and sustained attention, reaction time, and various other driving performance metrics (e.g., centerline and road-edge crossings). Moreover, alcohol tends to lead to more reckless driving, as evidenced by increasing speed (or more variable speed: standard deviation of speed, SDSP), shortening following distance to lead vehicles, or running red lights or stop signs, all of which may increase the likelihood of accidents. Impairment on these driving performance outcomes is typically observed at a BAC of 0.05% (or lower) and generally increases in a dose-orderly fashion. High Δ9-THC cannabis also negatively impacts simulated driving performance (Martin et al., 2013; Jongen et al., 2016; Irwin et al., 2017; Van Dijken et al., 2020). As with alcohol, high Δ9-THC cannabis reliably increases lane weaving (i.e., SDLP); SDLP has consistently been the most sensitive driving outcome measure following acute high Δ9-THC cannabis exposure (as with alcohol, high Δ9-THC cannabis reliably increases SDLP; Arkell et al., 2020; Marcotte et al., 2022). Likwise, SDLP and other measures of lateral control are particularly impacted by high Δ9-THC cannabis during controlled driving tasks that are more cognitively demanding than regular driving (e.g., divided attention or car following tasks; McCartney et al., 2021; Marcotte et al., 2022; Simmons et al., 2022; Thawer et al., 2022). Unlike alcohol, high Δ9-THC cannabis tends to lead to reduced driving speed (McCartney et al., 2021; Simmons et al., 2022; Thawer et al., 2022). Other driving outcomes are also negatively impacted by high Δ9-THC cannabis (e.g., reaction time, ancillary outcomes on divided attention or car following tasks), albeit in a less consistent fashion than SDLP and speed (McCartney et al., 2021). These inconsistent results are likely due to differences in Δ9-THC doses administered and dosing procedures (e.g., *ad libitum* vs. fixed dosing), and the types of simulations/scenarios used across studies. Though relatively few studies have administered cannabis and alcohol concurrently, co-use of alcohol and high Δ9-THC cannabis has been found to produce additive or synergetic driving impairment, again as evidenced most clearly by measures of lateral control (e.g., SDLP; Hartman et al., 2015; Simmons et al., 2022).

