For Part 1 and Part 2, a priori planned comparisons will be conducted to compare mean peak change-from-baseline scores for each outcome for: (1) alcohol alone (BAC 0.05%) to alcohol with cannabis (BAC 0.05% + 10 mg Δ9-THC and 25 mg Δ9-THC); and 2) cannabis alone (10 mg Δ9-THC and 25 mg Δ9-THC) to cannabis with alcohol (BAC 0.05% + 10 mg Δ9-THC and 25 mg Δ9-THC). Additionally, planned comparisons will compare impairment (e.g., DRUID scores, composite drive scores) between cannabis with alcohol (BAC 0.05% + 10 m g Δ9-THC and 25 mg Δ9-THC) to the positive control condition (alcohol alone: BAC 0.08%). Correlations will be conducted to assess the relations between DRUID and driving performance. Sensitivity and specificity analyses will be conducted to characterize the effectiveness of the DRUID for determining driving impairment. Specifically, we will plot the sensitivity (true positive rate) and specificity (true negative rate) of the DRUID at identifying impaired driving by comparing various DRUID cutoffs to established cutoffs for driving simulator data that are indicative of clinically meaningful impaired driving in real-world settings (e.g., SDLP change-from-placebo ≥ 2.4 cm; Jongen et al., 2016). Sensitivity and specificity will be calculated as follows: sensitivity (100 × [TP/(TP + FN)]) and specificity (100 × [TN/(TN + FP)]).

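### Car-following modulus is best at 1, but the planned peak change from baseline gives it no worse direction, and reading values above 1 as tailgating does not hold on the task's own figures

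*Protocol article*

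**What the plan says.** The text of section 2.7.3 that follows Figure 3 lists modulus among the primary measures of the car-following task, together with SDLP, response delay and coherence. It puts the ideal at 1. On the upper side of that ideal, the stated reading is that "values greater than 1 indicate the participant generally drove faster than the lead vehicle, which indicates tailgating behavior". On the lower side, the driver is taken to have been the slower of the two, with no further gloss.

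The same section gives the task's geometry: "This task commences when a vehicle appears about 300 ft in front of the participant’s vehicle". The task lasts 5 minutes, the lead car's speed varies sinusoidally between 50 and 70 mph, and the driver is told to hold a constant distance.

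Section 2.14 sets the planned comparisons (alcohol alone against co-use, and cannabis alone against co-use) on "mean peak change-from-baseline scores for each outcome". No exception is made for an outcome whose best value lies in the middle of its range. Drives take place at baseline and at 1.5, 3.5, 5.5 and 7.5 h (section 2.6), so the peak is chosen from four post-dose values.

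**The concern.** There are two linked problems.

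**Direction.** A peak change needs a worse direction. SDLP has one; modulus as described does not. The highest value, the lowest value and the largest departure over the four post-dose drives are different quantities, and the stated rule does not choose between them. A change of a given size can be an improvement or a deterioration, depending on which side of 1 the participant started. If some participants speed up and others slow down under the same condition, the mean change can be near zero although matching has become worse.

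**Interpretation.** Tailgating is a statement about distance. Modulus is described as a match of speeds. If every value above 1 is reported as tailgating, the trial could claim a safety-relevant behaviour that the measure does not show.

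**Working it through.** **1. What the change score can tell.** Take departure from 1 as the loss of matching.

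| Baseline | Post-dose | Change | Change in \|modulus - 1\| |
|---|---|---|---|
| 0.9 | 1.0 | +0.1 | -0.1 (better) |
| 1.0 | 1.1 | +0.1 | +0.1 (worse) |

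The two changes are equal, with opposite meanings. A participant with baseline 1.00 who records 1.10 at one drive and 0.90 at another has a peak of +0.10 if the maximum is taken and -0.10 if the minimum is taken. If the largest absolute change is taken, the two tie.

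**2. Modulus as a ratio of mean speeds.** Inputs from section 2.7.3: gap 300 ft, duration 300 s, lead speed 50 to 70 mph. A sinusoid averages 60 mph = 88 ft/s, so the lead car covers 88 × 300 = 26,400 ft.

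- Gap closed over the task = (m - 1) × 26,400 ft.
- Largest ratio before contact: m = 1 + 300/26,400 = 1.0114. Varying the gap over 250 to 400 ft and the mean speed over 50 to 70 mph gives 1.008 to 1.018.

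| Ratio m | Gap closed (ft) | Gap at end (ft) | Time gap at 88 ft/s |
|---|---|---|---|
| 1.002 | 53 | 247 | 2.8 s |
| 1.005 | 132 | 168 | 1.9 s |
| 1.010 | 264 | 36 | 0.4 s |
| 1.02 | – | contact at 170 s | – |
| 1.05 | – | contact at 68 s | – |

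The end gap stays above 2 s (176 ft) until the ratio reaches about 1 + 124/26,400 = 1.0047. So the smallest values above 1 do not show close following, and values above about 1.011 cannot be sustained for the whole task. There is no matching lower limit: a ratio of 0.95 simply ends 1,620 ft behind.

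**3. Modulus as an amplitude gain.** Lead and follower paths were simulated at 0.1 s steps, with a lag of 2 s and a 30 s or 60 s period. Gains of 1.2 and 1.5 both leave the ratio of mean speeds at 1.000. At gain 1.2 the gap never falls below 233 ft (233/88 = 2.6 s). A gain above 1 therefore means neither faster driving on average nor, by itself, tailgating.

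**4. Modulus as a mean of instantaneous ratios.** A driver at a constant 60 mph scores 1.014 while the gap stays between 300 and 440 ft (30 s period). This too is a value above 1 without tailgating.

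**5. Averaging across participants.** The article prints no effect size or SD for modulus, so these inputs are assumed: individual shift 0.10, between-person SD 0.05, SD of the within-session change 0.10, n = 32, and a two-sided paired t-test of active against placebo on one post-dose drive (10,000 runs). Shifts of this size are feasible upwards only if modulus is not a mean-speed ratio (step 2).

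| Share shifting up | Signed change: power | Change in \|modulus - 1\|: power |
|---|---|---|
| 50% | 5% | 53% |
| 70% | 26% | 53% |
| 90% | 80% | 53% |
| 100% | 97% | 54% |

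With between-person SD 0.10, or with the shift and both SDs at 0.05, power for the folded measure is only about 25% throughout.

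**The case against.** Section 2.14 does not use the word signed, and a condensed article may leave scoring rules for single variables to a fuller plan. That is fair: signed analysis is an inference. What stands is that the article does state one rule for every outcome, and that rule is undefined for this one.

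A reader might infer from the Introduction ("Unlike alcohol, high Δ9-THC cannabis tends to lead to reduced driving speed") that the two drugs cancel on modulus under co-use. The documents do not support this. That sentence is about speed. It predicts the direction of modulus only if modulus is a mean-speed ratio, and then upward room ends at about 1.011. If modulus is an amplitude gain, the sentence says nothing about it. Nor would opposite effects vanish from the planned contrasts. With illustrative values of alcohol 1.10, cannabis 0.90 and co-use 1.00, co-use differs by -0.10 from alcohol and by +0.10 from cannabis. Folding would not help there: co-use would score 0 and look better than either drug alone.

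A reader might also call the tailgating reading impossible. It is not. A mean-speed ratio of 1.010 ends 36 ft behind the lead car, which is close following. The fault is applying the reading to every value above 1.

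Finally, it is tempting to say that the Composite Drive Score would count slowing as improvement. Section 2.7.8 names SDLP and coherence from this task as examples, not modulus, so that is conditional on modulus being included.

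**Conclusion.** The point holds in a limited form. For an outcome that is best at 1, the stated peak change from baseline does not separate better from worse matching, and it averages out participants who move in opposite directions. The equation of values above 1 with generally faster driving and tailgating is not tenable as a general rule. Under a mean-speed ratio it could apply only to a narrow band below about 1.011 (1.008 to 1.018 over the gaps and speeds tried). Under an amplitude gain it does not follow.

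The kinematic limit rests on the article's own figures and a mean lead speed of 60 mph. The power figures rest wholly on assumed shifts and SDs. They show that either form of the outcome can be the weaker one, so they do not justify replacing the signed value. SDLP, response delay and coherence remain as measures of the same task. The consequence is therefore confined to modulus and what is concluded from it.

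**What to change.** - State whether modulus is a ratio of mean speeds or an amplitude gain, and correct the tailgating sentence to match.
- Draw any conclusion about tailgating from headway distance to the lead vehicle.
- Analyse |modulus - 1| as the measure of impaired matching, alongside signed modulus and not in its place. Fix before unblinding how the peak is taken for each.
- If modulus enters the Composite Drive Score, use the folded form, because higher composite values are meant to be worse.

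The cost is some wording and one extra derived variable. The folded measure loses power when everyone shifts the same way (54% against 97% under the assumptions above), which is why both are kept. It also does not recover opposite drug effects that offset within one person, so the two should be read together.
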